**Analysis**

All data will be coded and entered to statistical software SPSS (version 23). Continuous variables will be presented as mean ± standard deviation while categorical variables will be presented as counts and percentages. The difference in the responses between the two groups will be examined using unpaired test t-test or Mann-Whitney U test for continuous variables and Chi-square (X2) test or Fisher’s exact test for categorical variables. The impact of the education on the inhaler technique, disease control, quality of life, and adherence within each group over time were examined using McNemar Test for categorical variables and Wilcoxon test for continuous/ordinal variables. All tests will be two-sided and statistical significance will be set at *p*-value ≤ 0.05. Intention to treat analysis will be adopted to handle missing data.

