**LITERATURE REVIEW**

Asthma and COPD, two chronic inflammatory conditions of the lungs, affect millions of people all over the world (WHO). Their prevalence is increasing in Jordan and COPD is still largely underdiagnosed and undertreated (20, 21).

Medications delivered through inhaler devices are the mainstay therapy for respiratory conditions (5).Inhaler devices require proper technique crucial for the optimal drug delivery and deposition in its site of action for both controller and reliever (rescue) medications (22). This however needs multiple, complex steps, some of which considered critical to the efficacy of the inhaled treatment, making inhaler devices difficult to use (5, 13).

Incorrect inhaler technique has been reported worldwide in asthma and COPD patients for pressurized metered dose inhalers and dry powder inhalers, with most of these patients being even not aware of having problems is using their device (1, 2, 23).In a recent study conducted in Jordan, only 35% of asthmatic patients demonstrated proper technique, while no studies investigated inhaler misuse in patients with COPD (9).

Poor technique has been associated with increased frequency of inhaler use and frequency of emergency department visits indicating a poorly controlled condition. It has also been associated with higher local and/or systemic side-effects, higher risk of exacerbation, increased use of oral corticosteroid and decreased quality of life in patients with asthma and COPD (22). In Jordan, a cross-sectional study showed that only one-third of asthmatic patients has controlled asthma while no data is available for COPD patients (24).

The GINA, GOLD and the British guidelines strongly address the importance of patient education on inhaler technique, considered crucial for the mastery of good inhaler technique and effective self-management of asthma and COPD (1, 2, 6, 10, 11). Despite its importance, suboptimal education has been reported (6).

Several are the studies that investigated the effect of patient education on the proper use of inhalers and disease control in asthma and COPD (25, 26).In particular, the Teach-To-Goal (TTG) intervention has been demonstrated to be more effective than the standard education usually provided to the patients at hospitals (single brief set of verbal step-by-step instructions) in improving inhaler technique, particularly for those with low health literacy (12, 13, 19, 25, 27).

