**Baseline assessment and outcomes:**

At baseline, data regarding demographics, asthma/COPD history, medication use including adverse effects, hospital admissions, and previous systemic corticosteroid use.

Inhaler technique as well as the level of asthma/COPD control, adherence to medication and the patients’ quality of life will be assessed at baseline.

Initially, all participants will be asked to use their inhaler in front of the clinical pharmacist and the proper technique will be assessed by the aid of standardized device-specific inhaler technique checklists (AstraZeneca Pharmaceuticals, GlaxoSmithKline, Boehringer Ingelheim Pharmaceuticals) translated into Arabic. Each checklist includes 9-10 steps, eight of them considered essential for the medication to reach the site of action. A score of 8/10 will be thus considered and classified as correct inhaler technique for all of them.

All participants will be assessed for their level of asthma or COPD control through validated Arabic version of the Asthma Control Test )ACT( or COPD assessment test (CAT) before intervention (38, 39).

Medication adherence and quality of life will be assessed by the Arabic versions of the validated 8-items Morisky medication adherence scale (MMAS) of the St. George’s respiratory questionnaire respectively before and after intervention (2, 40-42).

The primary outcome for this research project is to improve inhaler technique in patients with asthma and COPD. Secondary outcomes include increase the level of asthma and COPD control, improve medication adherence, and quality of life.

After collection of all information and assessment of parameters at baseline, patients will receive either the in-person education or the video-based teach-to-goal intervention. Participants will be then asked to use their inhaler as prescribed by the physician.

All patients will be followed up for 3 months, after which inhaler technique, level of asthma/ COPD control, adherence to medication and the patients’ quality of life will be assessed.

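### The between-arm tests make no use of the baseline values collected for every outcome: they are valid, but adjustment would add precision at almost no cost

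*Protocol*

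**What the plan says.** The Analysis section fixes the between-arm tests. For continuous outcomes: "The difference in the responses between the two groups will be examined using unpaired test t-test or Mann-Whitney U test for continuous variables". For the rest it names the "Chi-square (X2) test or Fisher’s exact test for categorical variables". None of these tests takes a covariate, and the section mentions no regression, ANCOVA, stratified test or comparison of change scores. Baseline values enter only the analyses of the education's effect "within each group over time were examined using McNemar Test for categorical variables and Wilcoxon test for continuous/ordinal variables", which do not compare the arms.

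The baseline data will exist. Under Baseline assessment and outcomes: "Inhaler technique as well as the level of asthma/COPD control, adherence to medication and the patients’ quality of life will be assessed at baseline". The same section repeats the measurements later: "All patients will be followed up for 3 months, after which inhaler technique, level of asthma/ COPD control, adherence to medication" and quality of life. It also states: "The primary outcome for this research project is to improve inhaler technique in patients with asthma and COPD".

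Study design and participants specifies simple randomization by odd and even numbers, without stratification. It sets no entry criterion on current technique for patients already using an inhaler for at least a month. The Literature Review reports that in a Jordanian study "only 35% of asthmatic patients demonstrated proper technique".

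**The concern.** Each outcome has a baseline measurement on the same scale, usually the most useful covariate available. A test that leaves it out has a larger standard error than necessary. If the arms happen to differ at entry, the estimate also carries part of that difference.

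The design does nothing to limit such differences. Allocation is unstratified across two diseases and five device types, and some patients may already use their inhaler correctly when they enter. The stake is greatest for the secondary scores, for which no sample size is given, and for the primary outcome if the true effect is smaller than planned.

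Because the protocol itself names the tests, this is a stated choice and not a detail left to a later analysis plan.

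**Working it through.** **1. The plan's own figure.** Inputs from the sample-size paragraph: 40% correct in the control arm at three months, an 80% increase, 95% power, 5% significance, 20% dropout. The Analysis section makes tests two-sided. Read as a relative increase, 0.40 × 1.8 = 0.72. With pooled variance, mean proportion 0.56:

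n = [1.96 × √(2 × 0.56 × 0.44) + 1.645 × √(0.40 × 0.60 + 0.72 × 0.28)]² / 0.32² = (1.376 + 1.093)² / 0.1024 = 59.5, so 60 per arm.

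60 × 1.2 = 72, the stated number. The planned comparison is therefore an unadjusted 40% versus 72%. After 20% dropout, 72 × 0.8 = 57.6, so 57 or 58 per arm remain.

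**2. Continuous scores.** Adjusting for baseline multiplies the variance of the between-arm contrast by 1 − r², where r is the baseline/follow-up correlation. The protocol gives no r, so a range is assumed. Power is for an assumed effect of 0.5 SD with 58 per arm. The detectable effect at 80% power is (1.96 + 0.842) × √(2/58) × √(1 − r²).

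| r | Variance factor | Variance cut | Power | Detectable effect (SD) |
|---|---|---|---|---|
| unadjusted | 1.00 | – | 76.8% | 0.52 |
| 0.3 | 0.91 | 9% | 80.6% | 0.50 |
| 0.5 | 0.75 | 25% | 87.5% | 0.45 |
| 0.6 | 0.64 | 36% | 92.0% | 0.42 |
| 0.7 | 0.51 | 49% | 96.5% | 0.37 |

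**3. Correct technique (binary primary).** Assumptions: 57 per arm, 35% correct at baseline, and a baseline odds ratio (OR) of 2, 4 or 8 for being correct at three months. These ORs correspond to binary correlations of about 0.16, 0.32 and 0.46. Simulated trials compared the unadjusted chi-square test with a Mantel-Haenszel test stratified by baseline technique.

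| Three-month rates | Unadjusted | OR 2 | OR 4 | OR 8 |
|---|---|---|---|---|
| 40% vs 72% (planned) | about 94% | 94–95% | about 96% | about 97% |
| 40% vs 60% (not in the protocol) | about 57% | 58–59% | about 61% | about 66% |
| 40% vs 40% (null) | about 5% | about 5% | about 5% | about 5% |

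**4. Chance imbalance.** With 58 per arm, the 95% range of the baseline difference in a score is ±1.96 × √(2/58) = ±0.36 SD. The part carried into the unadjusted three-month contrast is r times this: at r = 0.5, 0.5 × 0.36 = 0.18 SD at that limit.

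For technique at an assumed 35% baseline rate, the range is ±1.96 × √(2 × 0.35 × 0.65 / 58) = ±17 percentage points. At OR 4, a control rate of 40% splits into about 61% among those correct at baseline and 28% among the rest (0.35 × 0.61 + 0.65 × 0.28 = 0.40). A 17-point imbalance would then shift the contrast by about 17 × (0.61 − 0.28) = 6 points.

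**The case against.** **The unadjusted comparison is valid.** This stands in full. A reader might infer that these tests are biased or inflate false positives. They do not: type I error stays near 5%, and chance imbalance is already reflected in the unadjusted standard error.

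**The primary outcome hardly needs the gain.** This stands at the planned effect, where power is about 94% without adjustment and rises by at most about 3 points. The 5- to 10-point gains appear only at 40% versus 60%, which is not the protocol's planning effect.

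**Baseline may not be a strong predictor.** A reader might assume that it is, but no figure in the protocol shows it. For technique there is reason for doubt: both arms are taught and reassessed straight after baseline, over repeated cycles, which may weaken the link. The 35% figure comes from asthma patients only, and the protocol says no Jordanian data exist for COPD.

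**Imbalance does not pass through whole.** Correct. Only the fraction set by the correlation carries over.

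**The word for what is compared is undefined.** If "responses" meant change scores, baseline would be used. The text does not say so, and the change score has variance factor 2(1 − r) against 1 − r² for ANCOVA. The difference is (1 − r)², never negative: at r = 0.5, 1.00 against 0.75.

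**Covariates belong in the statistical analysis plan.** Often so, but here the protocol has already named covariate-free tests, so its wording should change.

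**Conclusion.** The point holds as a free improvement. The planned between-arm tests are valid but leave collected information unused. The gain is potentially material for the secondary scores, with a variance cut of 9% to 49% over r = 0.3 to 0.7. It is small for the primary outcome at the planned effect (about 94% to at most 97%) and larger if the true effect is smaller (about 57% to between 58% and 66% at 40% versus 60%).

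All these sizes rest on assumed correlations or odds ratios, an assumed 35% baseline rate and 57 or 58 completers per arm. The documents do not support a claim that the primary analysis is invalid, or that it is underpowered at its own planning effect for want of adjustment.

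**What to change.** Amend the between-arm part of the Analysis section:

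- **Primary.** Compare correct technique at three months between arms, adjusted for baseline technique and diagnosis. Use either a Mantel-Haenszel risk difference stratified by these two factors or logistic regression followed by standardization to a risk difference. Report it with a 95% CI.
- **Adherence and quality of life.** ANCOVA of the three-month score on arm, with the baseline score and diagnosis as covariates.
- **Disease control.** ACT and CAT are different instruments for different diseases. Fit a separate ANCOVA within each disease, with the baseline score as the only covariate, since diagnosis is constant there.
- **Timing.** Fix the covariates before any outcome data are seen. Keep the simple tests as supportive analyses.

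This needs no extra patients, visits or data. The cost is the change of wording and one further analysis step for the primary outcome, because a logistic model or a Mantel-Haenszel odds ratio does not by itself give a risk difference.

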**Objectives:**

The objectives of the present research proposal are:

- To assess inhaler techniques, level of asthma/COPD control, medication adherence, quality of life and asthma- and COPD-related knowledge among Jordanian patients with asthma or COPD.
- To evaluate and compare the effectiveness of two methods of patient education on mastering inhaler technique among Jordanian patients with asthma and COPD; the traditional in-person TTG education and the video-based TTG one. This will be done immediately after the intervention and three months later.
- Assess the impact of the two interventions at the level of asthma and COPD control, medication adherence and quality of life on Jordanian patients with asthma and COPD after 3 months of the intervention.
- To evaluate the impact of the video-based TTG patient education on asthmatic and COPD patients with low literacy in comparison to high literacy patients.

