**METHODOLOGY**

**Study design and participants:**

A prospective, open label, randomized controlled trial will be conducted at the Jordan University Hospital (JUH) in cooperation with [name] [name] from the respiratory team at (JUH), the Jordan Hospital and others public hospitals. An ethical approval will be obtained from the institutional review boards of the JUH, the Jordan Hospital and the Ministry of Health before starting the study.

All eligible patients between 17 and 80 years old attending the respiratory outpatient or the inpatient respiratory clinic in the hospitals will be invited to join the study and asked to sign a consent form before their participation.

Inclusion criteria include patients with an established asthma or COPD diagnosis by a respiratory physician, who were started on inhaler/s (pressurized metered dose inhaler (pMDI), turbohaler, accuhaler, handihaler, and soft mist inhaler) for a minimum of one month and are expected (as prescribed) to continue using their inhalers for a minimum of three months. Immunocompromised patients, patients who have difficulty in communication due to special needs or very severe clinical presentation will be excluded from the study.

Participants will be randomized into two groups. Simple randomization will be adopted; odd number for the educational intervention and even number for control.

Later each group will be provided, by a clinical pharmacist, with a different inhaler technique educational intervention (Non-invasive). The control group patients will receive an in-person TTG education consisting of a brief counseling on the proper use of inhalers followed by assessment. This cycle of assessment and counseling will be repeated up to three times if necessary, until the patient demonstrated correct technique on all steps.

Patients in the intervention group will receive a video-based teach-to-goal intervention on the proper inhaler technique using videos provided by the originator company of each inhaler type. Patients will be asked to watch a video (3-5 minutes in length) followed by assessment. If the assessment reveals incorrect use of the inhaler, the participants will be prompted to watch the video again and repeat until mastery will be demonstrated. If needed, the correct answer will be provided following 3 incorrect attempts. Patients in this group will be provided the video as a multimedia file to access it whenever they need re-education regarding their inhaler technique.

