Based on published data, around 40% of Jordanian patients demonstrated proper inhaler technique after 3 months they have been provided the “Show-and-Tell” intervention, which is very similar to the TTG intervention (9). Thus, in order to detect 80% increase in the number of patients with correct use of inhaler, and accounting for 20% dropouts during the study period a sample size of 72 participants is required in each group at 95% statistical power and 5% significance level (Clincal.com).

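### The Analysis section attaches the impact of education to before-after tests within each arm, although both arms are educated and only the between-arm comparison is randomised

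*Protocol*

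**What the plan says.** The Analysis section names two sets of tests.

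- **Between groups:** unpaired t-test or Mann-Whitney for continuous variables, chi-square or Fisher's exact for categorical ones, applied to the difference in responses. The sentence gives no outcome and no time point.
- **Within groups:** McNemar for categorical variables, Wilcoxon for continuous or ordinal ones. These are to examine "The impact of the education on the inhaler technique, disease control, quality of life, and adherence within each group over time". The four outcomes listed are the primary outcome and all the secondary outcomes in Baseline assessment and outcomes.

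The section does not say which set carries the trial's conclusions.

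Under Objectives, the second objective asks for a comparison of the two teaching methods on inhaler technique. The third reads "Assess the impact of the two interventions at the level of asthma and COPD control, medication adherence and quality of life" and does not ask for a comparison. Study design and participants gives in-person teach-to-goal education to the control group and video-based teach-to-goal education to the intervention group. It recruits patients "attending the respiratory outpatient or the inpatient respiratory clinic".

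**The concern.** Randomisation makes the two arms comparable with each other. It does nothing for the comparison of an arm with its own baseline. With no uneducated arm, a three-month change within an arm mixes any effect of education with the passage of time, concurrent treatment, being tested repeatedly and regression to the mean. Because inpatients are eligible, recovery is a further possible source of change in disease control and quality of life. A small McNemar or Wilcoxon p-value shows that something changed, not that education changed it.

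The only sentence in the Analysis section that lists the outcomes, and the only one that speaks of impact, is the within-arm sentence. Its wording also lies close to that of Objective 3. An author following the text could report a significant before-after change in control, adherence or quality of life as the effect of education, or of one method. The design cannot support either statement.

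**Working it through.** **1. Which comparison was the trial sized for?** The inputs are in the sample-size paragraph at the end of Study design and participants and in Analysis:

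- control proportion 0.40: "around 40% of Jordanian patients demonstrated proper inhaler technique after 3 months"
- effect: "detect 80% increase in the number of patients with correct use of inhaler", read as relative, so 0.40 × 1.8 = 0.72
- "95% statistical power and 5% significance level", with two-sided tests according to Analysis
- "accounting for 20% dropouts during the study period"
- stated result: 72 per group

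Two-proportion formula with pooled variance under the null and no continuity correction, where p̄ = (0.40 + 0.72)/2 = 0.56:

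n = [1.96·√(2·0.56·0.44) + 1.645·√(0.40·0.60 + 0.72·0.28)]² / 0.32²
= (1.376 + 1.093)² / 0.1024 = 59.5, so 60 per arm. Then 60 × 1.2 = 72.

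Unpooled variance: n = (1.96 + 1.645)² × 0.4416 / 0.1024 = 56.04, so 57 per arm. Then 57/0.8 = 71.25, so 72.

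Both routes give the stated figure. (The pooled 60 divided by 0.8 would give 75, and reading the effect as 40% to 80% gives 36, then 45, which does not match.) The trial was sized for a between-arm comparison of proportions.

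**2. What power does that comparison have after dropout?** 72 × 0.8 = 57.6, taken as 58 analysed per arm.

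Power = Φ{[0.32 − 1.96·√(0.4928/58)] / √(0.4416/58)} = Φ{(0.32 − 0.1807)/0.0873} = Φ(1.597) = 0.945.

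With all 72 per arm analysed it is 0.978. Resting the conclusions on the between-arm contrast needs no more patients.

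**3. What does each planned comparison identify?**

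| Comparison | What it contains |
|---|---|
| Within one arm, baseline to three months | Education + time + concurrent treatment + repeated testing + regression to the mean + possible recovery |
| Between arms at three months | Video against in-person teaching; the shared components balance in expectation under randomisation |
| Education against none | Not identified, because every participant is educated |

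**4. Illustration only: what if the two within-arm p-values were set against each other?** The protocol does not state this rule. If both arms have the same true change and each within-arm test has power P, exactly one arm is significant with probability 2P(1 − P). That is 0.50 at P = 0.5, 0.42 at P = 0.7 and 0.32 at P = 0.8.

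A simulation agrees. It used 20,000 runs, 58 per arm, 35% correct at baseline (the Introduction's figure for asthma patients in Jordan), assumed equal final rates in both arms, and assumed independence of the two measurements:

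| Final rate, both arms | McNemar significant in a given arm | Exactly one arm significant | Between-arm test significant |
|---|---|---|---|
| 55% | 50% | 50% | 5.0% |
| 60% | 70% | 41% | 5.0% |
| 72% | 97% | 6% | 5.5% |

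The within-arm tests reject often whatever caused the change. The between-arm test holds close to its 5% level.

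**The case against.** The strongest reply is that the between-arm analysis is already there. The sentence just before the within-arm one plans it, nothing restricts it to inhaler technique, and the sample size is built on it. The within-arm tests are expressly confined to each group over time. Secondary before-after tests beside a between-arm test are not an error in themselves, and outcome-by-outcome detail is often left to a statistical analysis plan.

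Most of this stands, and it rules out several stronger readings that a reader might infer:

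- *That the plan cannot compare the two methods.* It can; the preceding sentence does so.
- *That Objective 3 would be answered only with before-after data.* The between-group sentence covers continuous and categorical responses, so control, adherence and quality of life fall within it on a natural reading.
- *That the methods will be compared by significance in one arm and not the other.* No section says so, and the figures in step 4 depend on assumed effects.
- *That inpatients enter at a low point and will improve.* The protocol gives no share of inpatients, requires at least one month on an inhaler and excludes very severe presentations. Recovery is possible, not established. It also bears on control and quality of life more than on technique, and eligibility does not select for poor technique.

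What the reply does not remove is the attribution. Calling the within-arm result the impact of education is a choice stated in the protocol, not a detail deferred to another document. It is unsupported for outpatients as well as inpatients.

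**Conclusion.** The point holds in limited form, at moderate severity. The Analysis section gives a causal label, for the primary and all secondary outcomes, to tests that cannot carry it, and it leaves open which tests support the conclusions. The randomised comparison is planned and adequately sized: about 94.5% power with 58 analysed per arm, on the protocol's own 40% and a relative reading of its 80% increase. What is at risk is the interpretation of the results.

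This conclusion rests on the design alone: two educated arms and no uneducated one. It does not depend on the inpatient share or on the simulation. No size can be put on the bias in a within-arm change, because the documents give no estimate of change without education. The discordance figure of up to 50% illustrates a rule the protocol does not contain and is not an error rate of this trial.

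**What to change.** In the Analysis section:

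1. State that conclusions on inhaler technique, disease control, adherence and quality of life, including those under Objective 3, rest on the between-arm contrast at three months, given as a risk difference or mean difference with a 95% confidence interval.
2. State that this contrast answers video-based against in-person teach-to-goal education, and not education against none.
3. Relabel the within-arm analyses as descriptive change over time, and say that neither an effect of education nor a difference between the methods will be concluded from them. Dropping their p-values is good reporting practice but secondary to the relabelling.

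The cost is wording only. The sample size, visits and data collection do not change. The trial gives up a claim about education as such, which its design could not have supported.
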